### Measurements

Primary and secondary endpoints will be measured at baseline (week 0), post-intervention (week 13) and through-out the 12-week on-trial period (Table 1).

**Table 1 Tab1:** Assessments of study feasibility

Measures	Time of collection
Recruitment and completion	
- Referred patients	Trial completion
- Eligible patients	Trial completion
- Enrolled patients	Trial completion
- Eligibility rate	Trial completion
- Recruitment rate	Trial completion
- Trial completions	Trial completion
- Patient withdrawals	Trial completion
- Patient drop-outs	Trial completion
- Trial contamination	Trial completion
Patient safety (control arm)	
- Number of adverse events	Tri-weekly record
- Severity of adverse events	Tri-weekly record
- Number of skeletal complications	Tri-weekly record
Patient safety (intervention arm)	
- Number of adverse events	At each exercise session
- Severity of adverse events	At each exercise session
- Number of skeletal complications	At each exercise session
Program tolerance (intervention arm)	
- Pre-sessional bone pain	At each exercise session
- Pre-sessional fatigue	At each exercise session
- Sessional rating of perceived exertion	At each exercise session
- Sessional tolerance	At each exercise session
Program adherence (intervention arm)	
- Number of completed sessions	Post intervention
- Number of missed sessions	Post intervention
Program compliance (intervention arm)	
- Prescribed vs. actual exercise completed (for each exercise mode).	Post intervention
- Percent of total volume completed (for each exercise mode).	Post intervention

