#### Primary Endpoint

##### Feasibility

Study and programme feasibility will be quantified through a series of multi-item categories including patient recruitment and trial completion, patient safety and tolerance and program adherence and compliance (Table 2). Programme safety will be assessed by recording the incidence and severity (grading) of adverse events and/or skeletal complications [18] throughout the on-trial period for the intervention and control arms in accordance with the common terminology criteria for adverse events (CTCAE) v5.0 criteria. Skeletal complications will include heightened bone pain at sites of known bone metastases and/or pathological skeletal fractures. The nature, severity and impact of bone pain will be examined using the Functional Assessment of Chronic Illness Therapy (FACIT) bone pain questionnaire at baseline and post intervention.

**Table 2 Tab2:** Schedule of assessments at baseline and post intervention

Measures	Baseline	Post intervention
Tumour morphology (off-site)		
- MRI: T1-axial	X	X
Tumour biomarkers		
- Blood: HIF-1α, TGF-β	X	X
Anthropometry		
- Height (cm)	X	
- Weight (kg)	X	X
- Waist circumference (cm)	X	X
- Hip circumference (cm)	X	X
- Femoral length (mm)	X	
- Tibial length (mm)	X	
- Body mass index (kg/m^2^)	X	X
- Waist-to-hip ratio	X	X
Body composition		
- DXA: whole-body, spinal, hip	X	X
- pQCT: femoral, tibial	X	X
Physical assessments		
- NeuroCom Balance Test	X	X
- 1RM Strength Test (Leg Extension)	X	X
- 400 m Walk Test	X	X
- Timed Up and Go Test	X	X
Other biomarkers (off-site)		
- Blood: P1NP, ALP, CRP, fasting glucose and lipids	X	X
- Urine: NTx	X	X
Questionnaires		
- Demographic and health history	X	
- Concomitant medications	X	X
- Health-related quality of Life (SF-36)	X	X
- Cancer-specific quality of life (EORTC: QLQ30, BR23)	X	X
- Bone Pain (FACIT-BP)	X	X
- Brief Symptom Index (BSI-18)	X	X
- Insomnia Severity Index (ISI)	X	X
- Godin Leisure-time Exercise	X	X
Exercise programme		
- Clinic exercise record sheet (prescribed vs. actual)	At each exercise session	
- Home exercise record sheet (prescribed vs. actual)	At each exercise session	
- Pre-session bone pain, muscle soreness and fatigue (VAS)	At each exercise session	
- Post-session rating of perceived exertion and tolerance (VAS)	At each exercise session	

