*Abbreviations: HIF-1α* hypoxia-inducible factor 1-alpha, *TGF-β* transformation growth-like factor beta, *DXA* dual-energy x-ray absorptiometry, *pQCT* peripheral quantitative computed tomography, *P1NP* amino-terminal propeptide of type 1 procollagen, *NTx* amino-terminal collagen type-1 telopeptide, *ALP* alkaline phosphatase, *CRP* C-reactive protein, *SF-36* Short Form-36, *EORTC* European Organisation for Research and Treatment of Cancer, *FACIT-BP* Functional Assessment of Chronic Illness Therapy-Bone Pain, *VAS* visual analogue scale

Programme tolerance, adherence and compliance will be assessed in the intervention arm only. Specifically, programme tolerance will be quantified by routinely measuring pre-session bone pain, muscle soreness and general fatigue at each exercise session by visual analogue scale (VAS, 0–10) and by recording post-session rating of perceived exertion (Borg scale, 0–10) and post-session tolerance (VAS, 0–10) after each exercise session. Programme adherence and compliance will be assessed using an exercise diary completed by the patient at all clinic-based and home-based exercise sessions to record volume of resistance training (weight lifted (kilogrammes), sets and repetitions), aerobic training (intensity (level), duration (minutes), speed (revolutions per minute), heart rate (maximum and average) and rating of perceived exertion), flexibility training (repetitions and hold time (duration)) and isometric training (repetitions and hold time (duration)) completed. These data will be compared to the prescribed and individualised exercise programme provided to each patient in order to establish programme adherence (completed versus missed sessions) and compliance (prescribed versus actual exercise completed for each training mode (resistance, aerobic, flexibility and isometric)).

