### Exercise programme

Participants assigned to the exercise arm will be required to participate in a modular, multi-modal exercise programme (M3EP), which includes spinal isometric training (SIT) for 12 weeks. The combined M3EP-SIT programme requires participants to attend three clinic-based exercise sessions each week spanning 60 min in duration (including warm up and cool down), supervised by an accredited exercise physiologist (AEP; Exercise and Sport Science Australia). Participants will also be asked to perform the SIT portion of the programme during two additional home-based exercise sessions each week spanning 15 min in duration. During combined M3EP-SIT sessions, spinal isometric training will be provided first, followed by the modular multi-modal exercise programme (Table 3).

**Table 3 Tab3:** Weekly distribution of testing, M3EP and SIT exercise sessions across the exercise intervention

	Monday	Tuesday	Wednesday	Thursday	Friday	Saturday	Sunday
Week 0	Baseline testing						
Week 1 to Week 2	SIT	–	SIT	–	SIT	REST	REST
	M3EP		M3EP		M3EP		
Week 3 to Week 12	SIT	SIT	SIT	SIT	SIT	REST	REST
	M3EP		M3EP		M3EP		
Week 13	Post-Intervention Testing						

Clinic exercise sessions occur on Monday, Wednesday and Friday; home isometric exercise sessions occur on Tuesday and Thursday. Spinal isometric exercises are provided at the start of all clinic exercise sessions (following a general warm up). Home-based SIT starts from week 3 onwards to enable appropriate familiarisation and training during the first 2 weeks of the programme

*Abbreviations*: *SIT* spinal isometric training (15 min), *M3EP* modular multi-modal exercise programme (60 min)

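### Table 1 collects the same safety measures on different triggers in the two arms, which puts the between-arm safety comparison at risk of ascertainment bias of unknown size and direction

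*Protocol article*

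**What the plan says.** The Feasibility section makes safety part of the primary endpoint, whose components are "patient recruitment and trial completion, patient safety and tolerance and program adherence and compliance". Adverse events and skeletal complications are to be graded by CTCAE v5.0 and recorded "throughout the on-trial period for the intervention and control arms".

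Table 1, under Measurements, sets the collection times for three safety measures: number of adverse events, their severity, and number of skeletal complications. For the control arm the entry is "Tri-weekly record". For the intervention arm it is "At each exercise session". The article does not say what tri-weekly means.

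The skeletal endpoint depends partly on symptoms: "Skeletal complications will include heightened bone pain at sites of known bone metastases and/or pathological skeletal fractures". Two bone-pain instruments are planned. The FACIT instrument is given to both arms, as a "bone pain questionnaire at baseline and post intervention". A 0–10 visual analogue scale before every session belongs to programme tolerance, and "Programme tolerance, adherence and compliance will be assessed in the intervention arm only".

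**The concern.** The control record follows the calendar. The exercise-arm record follows attendance. When the chance of recording an event differs by arm, a difference in counts mixes any effect of exercise with the opportunity to report.

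This matters because safety, together with trial completion, is the main part of the primary endpoint that can be compared between arms: tolerance, adherence and compliance exist in one arm only. The safety result also has consequences. Under Study design it helps decide whether controls are offered the programme, and under Dissemination plan whether later-phase trials follow.

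Two mechanisms pull in opposite directions. More frequent enquiry and repeated bone-pain prompts would raise recorded events in exercisers relative to controls. A record tied to sessions would lose events in a woman who stops attending, possibly because of the event itself.

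**Working it through.** The plan gives no figure for this point, so there is none to reproduce. The check counts scheduled collection points and then illustrates what a gap could do.

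**Inputs from the documents**
- Follow-up: 12 weeks on trial (Measurements).
- Clinic sessions: participants "attend three clinic-based exercise sessions each week spanning 60 min in duration", so 3 × 12 = 36 (Exercise programme).
- Home sessions: two a week from week 3 (Table 3 and its note), so 2 × 10 = 20.
- Exercise-arm total if home sessions count: 36 + 20 = 56.
- Arm size: 20 each (Participants).

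**Step 1: contacts under each reading of tri-weekly**

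| Reading | Control | Exercise, clinic only | Ratio | Exercise, clinic + home | Ratio |
|---|---|---|---|---|---|
| Three times a week | 3 × 12 = 36 | 36 | 1.0 | 56 | 1.56 |
| Every three weeks | 12 / 3 = 4 | 36 | 9 | 56 | 14 |

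Whether adverse events are recorded at home sessions is not stated. The diary described under Feasibility lists training volume only, so clinic-only is the safer count.

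**Step 2: transient events under the three-week reading (assumed durations)**

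If an event is noted only when present at a contact, the chance of capture is duration / interval, capped at 1. The interval is 21 days in controls and on average 7/3 = 2.33 days on a Monday, Wednesday and Friday schedule.
- 3-day episode: 3/21 = 0.14 against 1, ratio 7.
- 7-day episode: 7/21 = 0.33 against 1, ratio 3.
- 14-day episode: 14/21 = 0.67 against 1, ratio 1.5.
- Full recall since the last contact: ratio 1.

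The documents give neither episode duration nor recall, so the result is a range from 1 upwards and not an estimate.

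**Step 3: effect on a comparison with 20 per arm (assumed detection)**

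Take equal true risk, 95% detection in exercisers and lower detection in controls. The spurious risk ratio is the ratio of the detection rates. The rejection rate of a 5% Pearson chi-square test comes from exact enumeration at 50% true risk.
- Controls 80%: 0.95/0.80 = 1.19; rejection rate 0.07.
- Controls 60%: 0.95/0.60 = 1.58; rejection rate 0.20.
- Controls 40%: 0.95/0.40 = 2.375; rejection rate 0.47.

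Across true risks of 30% to 70% the rejection rate under unequal detection runs from 0.06 to 0.68. With 95% detection in both arms it is 0.053, 0.043 and 0.053 at true risks of 30%, 50% and 70%.

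**Step 4: what remains if contacts match**

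With 36 contacts in each arm, two differences are left. First, Table 1 has no safety collection point for an exerciser without a session, while the control record does not depend on one. The plan gives no rate of stopping exercise. Its attrition allowance, up to 25% or 0.25 × 20 = 5 women per arm, concerns leaving the trial and is only a rough guide. Second, bone pain is scored before each session in exercisers, while the only bone-pain instrument scheduled for controls is the questionnaire at the two test points.

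**The case against.** The strongest reply is that tri-weekly probably means three times a week. Clinic sessions fall on Monday, Wednesday and Friday, so a control record at that frequency would look like deliberate matching. This stands: the article does not support treating a large contact gap as fact.

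Several stronger readings also go beyond the documents:
- A reader might infer a roughly sevenfold inflation of exercise-arm events. That needs the three-week reading, a 3-day episode and no recall at all. None of these is in the article, and a periodic record can cover the interval since the previous one.
- A reader might infer that pre-session pain scores feed the skeletal-complication count. Table 1 lists them under tolerance, apart from the safety rows, and FACIT bone pain is measured alike in both arms. What stands is narrower: repeated prompting in one arm may raise reporting of heightened pain.
- A reader might infer that any event leading to a missed session is lost. It can be recorded at the next attended session, and Table 1 also counts missed sessions, withdrawals and drop-outs. The gap in the schedule concerns women who stop attending altogether. The Feasibility text intends recording over the whole on-trial period, but the Table 1 trigger does not secure it for them.
- A reader might infer that no safety result could be interpreted. Incidence among attending exercisers does not depend on the control schedule, and symptomatic fractures depend little on how often one asks. If closer surveillance raises exercise-arm counts, finding no excess is still informative for women who attend.

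Finally, no safety-specific test is named. Statistical analysis gives chi-square only for categorical variables in general, so the harm may fall on a descriptive comparison.

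**Conclusion.** The point holds as a risk of ascertainment bias in the between-arm safety comparison. The arm-specific triggers are stated in Table 1 and are not a detail left to a fuller document. The contact ratio lies between 1.0 and 14, depending on the meaning of tri-weekly and on whether home sessions count. The spurious risk ratios of about 1.2 to 2.4 and the rejection rates in the working rest on assumed detection and show only what such a gap could do.

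Under either reading, the missing record after attendance stops and the one-sided pain prompts remain. The net direction cannot be settled from the article. Low-grade events and pain are the outcomes most affected.

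**What to change.** - Define tri-weekly in Table 1.
- Collect adverse events and skeletal complications, with the same bone-pain question, in both arms on one prompted form and the same calendar days, whether or not a session is attended and whether or not the woman has stopped exercising.
- Base the between-arm safety comparison on these records only.
- Report session-level events and visual analogue scores separately, as exercise-arm safety and tolerance.

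The cost is an amendment to Table 1, one more form for the 20 exercise-arm women and a little extra contact time, with no new procedure. It is an inexpensive improvement, best made before data accrue, because events never asked about cannot be recovered at analysis.

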#### Primary Endpoint

##### Feasibility

Study and programme feasibility will be quantified through a series of multi-item categories including patient recruitment and trial completion, patient safety and tolerance and program adherence and compliance (Table 2). Programme safety will be assessed by recording the incidence and severity (grading) of adverse events and/or skeletal complications [18] throughout the on-trial period for the intervention and control arms in accordance with the common terminology criteria for adverse events (CTCAE) v5.0 criteria. Skeletal complications will include heightened bone pain at sites of known bone metastases and/or pathological skeletal fractures. The nature, severity and impact of bone pain will be examined using the Functional Assessment of Chronic Illness Therapy (FACIT) bone pain questionnaire at baseline and post intervention.

**Table 2 Tab2:** Schedule of assessments at baseline and post intervention

Measures	Baseline	Post intervention
Tumour morphology (off-site)		
- MRI: T1-axial	X	X
Tumour biomarkers		
- Blood: HIF-1α, TGF-β	X	X
Anthropometry		
- Height (cm)	X	
- Weight (kg)	X	X
- Waist circumference (cm)	X	X
- Hip circumference (cm)	X	X
- Femoral length (mm)	X	
- Tibial length (mm)	X	
- Body mass index (kg/m^2^)	X	X
- Waist-to-hip ratio	X	X
Body composition		
- DXA: whole-body, spinal, hip	X	X
- pQCT: femoral, tibial	X	X
Physical assessments		
- NeuroCom Balance Test	X	X
- 1RM Strength Test (Leg Extension)	X	X
- 400 m Walk Test	X	X
- Timed Up and Go Test	X	X
Other biomarkers (off-site)		
- Blood: P1NP, ALP, CRP, fasting glucose and lipids	X	X
- Urine: NTx	X	X
Questionnaires		
- Demographic and health history	X	
- Concomitant medications	X	X
- Health-related quality of Life (SF-36)	X	X
- Cancer-specific quality of life (EORTC: QLQ30, BR23)	X	X
- Bone Pain (FACIT-BP)	X	X
- Brief Symptom Index (BSI-18)	X	X
- Insomnia Severity Index (ISI)	X	X
- Godin Leisure-time Exercise	X	X
Exercise programme		
- Clinic exercise record sheet (prescribed vs. actual)	At each exercise session	
- Home exercise record sheet (prescribed vs. actual)	At each exercise session	
- Pre-session bone pain, muscle soreness and fatigue (VAS)	At each exercise session	
- Post-session rating of perceived exertion and tolerance (VAS)	At each exercise session	

*Abbreviations: HIF-1α* hypoxia-inducible factor 1-alpha, *TGF-β* transformation growth-like factor beta, *DXA* dual-energy x-ray absorptiometry, *pQCT* peripheral quantitative computed tomography, *P1NP* amino-terminal propeptide of type 1 procollagen, *NTx* amino-terminal collagen type-1 telopeptide, *ALP* alkaline phosphatase, *CRP* C-reactive protein, *SF-36* Short Form-36, *EORTC* European Organisation for Research and Treatment of Cancer, *FACIT-BP* Functional Assessment of Chronic Illness Therapy-Bone Pain, *VAS* visual analogue scale

Programme tolerance, adherence and compliance will be assessed in the intervention arm only. Specifically, programme tolerance will be quantified by routinely measuring pre-session bone pain, muscle soreness and general fatigue at each exercise session by visual analogue scale (VAS, 0–10) and by recording post-session rating of perceived exertion (Borg scale, 0–10) and post-session tolerance (VAS, 0–10) after each exercise session. Programme adherence and compliance will be assessed using an exercise diary completed by the patient at all clinic-based and home-based exercise sessions to record volume of resistance training (weight lifted (kilogrammes), sets and repetitions), aerobic training (intensity (level), duration (minutes), speed (revolutions per minute), heart rate (maximum and average) and rating of perceived exertion), flexibility training (repetitions and hold time (duration)) and isometric training (repetitions and hold time (duration)) completed. These data will be compared to the prescribed and individualised exercise programme provided to each patient in order to establish programme adherence (completed versus missed sessions) and compliance (prescribed versus actual exercise completed for each training mode (resistance, aerobic, flexibility and isometric)).

#### Secondary endpoints

##### Tumour morphology

Location of metastatic lesions will be initially identified through bone scans provided by the managing oncologist prior to referral to this study. Tumour morphology will be measured using axial T1-weighted magnetic resonance imaging (MRI) (1.5 T, Magnetom Essenza, Siemens, Victoria, Australia) in locations where osteolytic lesions have been identified in patients with bone metastases at either thoracic or lumbar spinal regions [75–78]. All patients will be scanned by the same radiologist using the same MRI machine and a standardised sequence and routine for scout and primary scan acquisition. Specifically, spinal bone metastases will be identified and confirmed using three preliminary axial scout scans in the sagittal plane to view the cervical, thoracic and lumbar regions, respectively (T2-weighted; imaging frequency = 63.66 Hz; slice thickness = 3.0–4.0 mm; spacing between slices = 3.6–6.0 mm; echo train length = 16–21; flip angle = 140–150°; acquisition matrix = 256\0\0\192 (cervical), 448\0\0\358 (thoracic) and 320\0\0\320 (lumbar)).

Primary scans of each affected vertebra will be performed in the transverse plane, capturing the vertebrae above and below to produce an image with three vertebrae in total (T1-weighted; imaging frequency = 63.66 Hz; slice thickness = 4.0 mm; space between slices = 4.2 mm; echo train length = 3; flip angle = 150°; acquisition matrix = 384\0\0\307). Following the acquisition of images, tumour morphology (volume (cubic millimetres) and intensity (watts per steradian (W/sr))) will be examined for each slice using ITK-Snap (V3.6.0) image analysis software [79] (Fig. 2). All images will be examined at the conclusion of the study by two independent researchers for consistency in analysis and to establish intra-rater and inter-rater reliability coefficients.

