**Fig. 2 Fig2:**
[figure not shown]
Example of magnetic resonance imaging (MRI) image acquisition. Left: cervical, thoracic and lumbar scout views stitched together with three osteolytic lesions identified at T5, T11 and L2. Top, middle: lumbar scout view at higher resolution with the L2 vertebra outlined. Bottom, middle: example data outputs provided by regional analysis. Right: slice by slice, cephalad to caudal, transverse view at each level of the L2 lesion, with an example colour map and tumoural analysis of one slice in isolation

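### T1-weighted MRI lesion intensity is given in an optical unit (W/sr) and is not a calibrated quantity for comparing baseline with week 13; tumour volume is unaffected

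*Protocol article*

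**What the plan says.** All of this is in the protocol article.

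- **Modality** (Tumour morphology): "Tumour morphology will be measured using axial T1-weighted magnetic resonance imaging (MRI") at 1.5 T.
- **Measures** (same section): volume in cubic millimetres and, for the signal, "intensity (watts per steradian (W/sr))) will be examined for each slice", using ITK-Snap.
- **Acquisition** (same section): "All patients will be scanned by the same radiologist using the same MRI machine and a standardised sequence and routine". Two independent researchers examine the images at the end of the study, with reliability coefficients. No reference tissue or signal normalisation is described.
- **Coverage** (same section): "Primary scans of each affected vertebra will be performed in the transverse plane, capturing the vertebrae above and below", so each image holds three vertebrae. The legend of Fig. 2 describes an example patient "with three osteolytic lesions identified at T5, T11 and L2".
- **Timing** (Measurements): week 0 and week 13.
- **Analysis** (Statistical analysis): *t* test and group × time repeated measures ANOVA, or ANCOVA.
- **Sample size** (Participants): counted in subjects, 16 per group for an effect size of at least 1.0.

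**The concern.** Watts per steradian describes optical power emitted into a solid angle, and a T1-weighted image does not measure that. Its pixel values are in arbitrary units, and their scale depends on coil position, receiver gain and reconstruction at each session. A physical unit presents the signal as calibrated, as if a number from week 0 and a number from week 13 lay on one scale.

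If absolute intensity is compared between visits, each patient's change is the tumour change mixed with a change of scale. There is no reason for the scale to move in favour of one arm, so the expected harm is noise and poor interpretability, not bias. Intensity is one of the two morphology measures serving the second aim, preliminary efficacy against tumour growth in target spinal lesions, and the results are meant to inform phase II and III trials.

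A secondary matter is that readings are taken slice by slice and at each affected vertebra, while the named tests need one independent value per patient per visit. The article does not state the link between the two.

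**Working it through.** **1. The plan's own figure.** Inputs from Participants: effect size d = 1.0, two-sided alpha 0.05, power 80%.

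n per arm = 2 × (1.96 + 0.842)² / d² = 15.7, so 16. The stated 16 reproduces by the normal approximation. The *t*-based calculation gives 16.7, so 17, with 78.1% power at 16. The count is of patients, and no stated figure depends on the MRI unit.

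**2. What session scaling does to intensity.** Write the recorded signal at visit v as S_v = g_v × I_v, where I_v is the lesion signal on a fixed scale and g_v is the session's scale factor. Then

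log(S_13/S_0) = log(I_13/I_0) + log(g_13/g_0).

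The second term has nothing to do with the tumour. Let σ be the between-patient SD of the true log change, τ the SD of the scaling term, and r = τ/σ. If the two are independent, the variance is σ²(1 + r²), and a true standardised effect of 1.0 becomes 1/√(1 + r²). Power at 16 per arm is Φ(d × √8 − 1.96). The article gives no value for r, so these rows are assumptions:

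| r (assumed) | observed d | power, 16 per arm | n per arm for 80% |
|---|---|---|---|
| 0 | 1.00 | 81% | 16 |
| 0.25 | 0.97 | 78% | 17 |
| 0.5 | 0.89 | 72% | 20 |
| 1 | 0.71 | 52% | 32 |

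**3. What a reference ratio does.** If reference tissue in the same scan has signal R_v = g_v × K, with K stable, then S_v/R_v = I_v/K. The shared factor g_v cancels and the log ratio of week 13 to baseline returns to log(I_13/I_0). The cancellation is incomplete if the scale varies across the image or if the reference is read with error, so the gain is largest where r is large.

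**4. Volume.** Volume comes from an outlined region and the slice geometry, in mm³. The factor g_v multiplies signal, not distance, so steps 2 and 3 do not apply to it.

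**5. The conditional case of pooled lesions.** Suppose m lesions per patient were entered as independent rows, with within-patient correlation ρ (assumed). The design effect is 1 + (m − 1)ρ, and the actual error of a nominal 5% test is about 2 × [1 − Φ(1.96/√design effect)]:

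| m | ρ | design effect | actual type I error |
|---|---|---|---|
| 2 | 0.2 | 1.2 | 7% |
| 2 | 0.5 | 1.5 | 11% |
| 2 | 0.8 | 1.8 | 14% |
| 3 | 0.2 | 1.4 | 10% |
| 3 | 0.5 | 2.0 | 17% |
| 3 | 0.8 | 2.6 | 22% |

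Simulation with 16 patients per arm agrees: 17% for m = 3 at ρ = 0.5, and 24% at ρ = 0.8. One mean per patient holds the error at 5.0 to 5.2%.

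**The case against.** The strongest reply has three parts.

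*The unit is only a label, and acquisition is well controlled.* One machine, one radiologist and a standardised sequence reduce session-to-session scaling, and two readers check the outlines. This stands in part: r may be at the low end of the table. But these controls do not fix coil position, receiver gain or reconstruction scaling at each visit, and agreement between readers of one image says nothing about the scale of that image. The article also never says that unnormalised signal will be differenced between visits. That is inferred from its silence, and normalisation may be described in a document not shown. The wrong unit, however, is printed.

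*The tumour endpoint as a whole is sound.* A reader might infer that MRI morphology cannot be compared across visits at all. The article does not support that. Volume has a valid unit and is the measure closest to tumour growth.

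*Reading by slice is not analysing by slice.* A reader might also infer that slices or lesions will be entered as separate observations, giving false evidence of tumour suppression. The article does not say so. Outlining each slice is the usual way to build a lesion volume, and the Fig. 2 legend's "slice by slice, cephalad to caudal, transverse view at each level of the L2 lesion" fits that. The sample size and the group × time analysis read as patient-level. The rule for combining lesions is a detail that an analysis plan may hold. Any inflation from pooling would also be two-sided, not specific to suppression. This part of the reply stands.

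**Conclusion.** The point holds for intensity. The stated unit is wrong for T1-weighted MRI, and absolute signal as defined is not a calibrated quantity for comparing week 0 with week 13. The consequence is added noise in both arms and a change that is hard to interpret. Its size is unknown: over an assumed r of 0.25 to 1, power for a true effect of 1.0 with 16 per arm would be 78% down to 52%, against 81% without scaling noise. This assumes that scaling is independent of arm and of tumour change.

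It does not extend to volume. Nor do the 7 to 24% error rates for two to three lesions per patient describe this plan. They apply only if lesions were pooled as independent, with an assumed within-patient correlation of 0.2 to 0.8 and the same number of lesions in every patient; the three-lesion count comes from one illustrative patient.

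The correction is worth making because it is cheap and the measure serves the efficacy aim. As this is a secondary endpoint of a pilot aimed mainly at feasibility and safety, it does not threaten the primary conclusions.

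**What to change.** 1. In Tumour morphology, replace watts per steradian with arbitrary units.
2. Analyse lesion signal as a ratio to a fixed unaffected reference tissue in the same scan. An unaffected neighbouring vertebra already lies in the three-vertebra image. If the neighbours are diseased, use another unaffected tissue such as disc. Name the reference region per patient at baseline and use the same one at week 13.
3. As a clarification only, state that the *t* test or ANOVA takes one value per patient per visit, for example the total volume of lesions identified at baseline, and that any lesion-level analysis carries a patient random effect.

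The cost is a few minutes of post-processing per scan to outline the reference region, plus wording. No further imaging or visits are needed, and the stated basis of 16 patients per group does not change.
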